## Abstract

**Background:**

Millions of people worldwide are exposed to dangerous levels of arsenic (above the WHO water standard of 10 ppb) in drinking water and food. Lack of nutritious foods exacerbates the adverse health effects of arsenic poisoning. The micronutrient selenium is a known antagonist to arsenic, promoting the excretion of arsenic from the body. Studies are in progress examining the potential of using selenium supplement pills to counteract arsenic toxicity. We are planning a clinical trial to test whether high-selenium lentils, as a whole food solution, can improve the health of arsenic-exposed Bangladeshi villagers.

**Methods/design:**

A total of 400 participants (about 80 families) will be divided into two groups via computer-generated block randomization. Eligibility criteria are age (≥14) years) and arsenic concentration in the household tube well (≥100 ppb).

In this double-blind study, one group will eat high-selenium lentils grown in western Canada; the other will consume low-selenium lentils grown in Idaho, USA. Each participant will consume 65 g of lentils each day for 6 months. At the onset, midterm, and end of the trial, blood, urine and stool, plus hair (day 1 and at 6 months only) samples will be collected and a health examination conducted including assessment of acute lung inflammation, body mass and height, and blood pressure. The major outcome will be arsenic excretion in urine and feces, as well as arsenic deposition in hair and morbidity outcomes as assessed by a biweekly questionnaire. Secondary outcomes include antioxidant status, lipid profile, lung inflammation status, and blood pressure.

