A number of studies have found an association between the detrimental effects of arsenic exposure and malnutrition [7–9], which is also a prominent health concern in the Bangladeshi population, especially in children [10]. Chen et al*.* found that the risk of developing arsenic-related skin lesions was greatly enhanced with low blood selenium. Selenium and arsenic work antagonistically in the body by competing in many biological functions [11]. In the blood, selenium interacts with arsenic to form a complex which is excreted in the bile [12], thereby lowering the arsenic body burden. Thus, higher selenium intake may be crucial to combat arsenic toxicity. Selenium levels in food are dependent on selenium bioavailability in the soil. Limited data are available on the selenium content of soils in Bangladesh. Initially it was found that agricultural soil in Bangladesh (*n* = 19) contains good selenium levels [13]. However, the authors determined that only 12 % of selenium was soluble, reducing the immediately available selenium to 0.12 μg/g. A ”nutritional selenium deficiency” in soil is < 0.5 μg/g soil [14]; therefore, Bangladeshi soil falls into the selenium deficient category. The US dietary recommended daily allowance (US-RDA) for selenium for an adult is 55 μg/day [15], and Spallholz et al*.* (2008) estimated that Bangladeshis consume about 26 μg/day [13], approximately half of the RDA.

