### Trial objectives

The hypothesis of the trial is that consumption of high-selenium lentils from Saskatchewan, Canada, will reduce the body burden of arsenic and decrease arsenic toxicity in a chronically arsenic-exposed Bangladeshi population compared to those consuming low-selenium lentils.

The primary objective was to perform a double-blind, randomized controlled trial to determine whether incorporation of high-selenium lentils into the daily diet, providing at least the RDA of Se (55 ug), can decrease the body burden of arsenic, evident by higher excretion in urine and/or feces and decreased deposition in hair, compared to the treatment group on low-selenium lentil consumption. Secondary objectives were to determine if consumption of high-selenium lentils:improves antioxidant statusreduces oxidative DNA damagechanges acute phase proteins as well as serum lipid levels in arsenic-exposed individualsdecreases arsenic-related lung inflammation measured using exhaled nitric oxide as an indirect indicatorimproves the body mass index (BMI) and blood pressure of arsenic-exposed individuals

Herein, we describe the design and methods protocol for our 3-year study now underway.

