## Methods/design

This trial protocol has been approved by the University of Calgary’s Conjoint Health Research Ethics Board (Ethics ID: REB13-1211-Mod3), the University of Saskatchewan’s Biomedical Research Ethics Board (Bio-No. 14-212), plus the Research Review Committee, the Ethics Review Committee, and the Data and Safety Monitoring Board (DSMB) of the International Centre for Diarrhoeal Disease Research, Bangladesh (Icddr,b) (Protocol No. PR-14013). Any changes to the trial protocol are communicated to the relevant parties and ethics boards. The trial will be reported according to SPIRIT (Standard Protocol Items: Recommendations for Intervention Trials) 2013 [21] (see Additional file 1). A summary of the trial according to the WHO Trial Registration Minimal Data Set is provided in Table 1 [22].

**Table 1 Tab1:** WHO Trial Registration Minimal Data Set according to Moja et al*.* [22]

Data	Information
Trial identification number	ClinicalTrials.gov NCT02429921
Trial registration date	April 21, 2015
Secondary IDs	REB13-1211 (CHREB, University of Calgary), PR-14013 (ERC, icddr,b)
Funding sources	Global Institute for Food Security (GIFS); Grand Challenges Canada - Stars in Global Health Round 5
Primary sponsor	[name], Faculty of Vet. Med, University of Calgary, Canada
Secondary sponsor	RR, icddr,b, Dhaka, Bangladesh
Responsible contact person	RR, icddr,b; [contact]
Research contact person	[name], Faculty of Vet. Med., University of Calgary; [contact]
Brief title of the study	High-selenium Lentils Versus Arsenic Toxicity
Official title of the study	Mitigating arsenic toxicity in Bangladeshi people by supplementing their diets with high selenium lentils
Country of recruitment	Bangladesh
Health problem studied	Chronic arsenic poisoning
Intervention	High-selenium lentils, control: low-selenium lentils
Key inclusion and exclusion criteria	Inclusion criteria: families with >100 ppb As in their well water; ages eligible for study: 14–75
	Exclusion criteria: As content of well water ≤100 ppb; ill health detected during initial recruitment health check
Study type	Double blind, parallel, block-randomized, controlled intervention trial
Trial start date	September 28, 2015
Target sample size	200 per treatment group (400 in total)
Recruitment status	Active
Primary outcome	Arsenic body burden: We will determine if high-Se lentil consumption will decrease the body burden of As by measurement of As excretion in urine and feces and deposition in hair

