### Sample size

We determined the sample size for this trial with an online power and sample size calculator (www.powerandsamplesize.com), based on a one-sided effect for arsenic concentration in hair.

Based on a previous intervention trial [28], in which arsenic-exposed participants received selenium-enriched yeast (100–200 μg/day, an amount two to four times higher than our dietary treatments), we calculated the sample size from their data generated after a 9-month intervention. Using the mean arsenic levels in hair of the control and selenium-treatment groups, Mean_A_ = 2.01 μg/g (±1.4) and Mean_B_ = 1.23 (±0.73), respectively, and a type I error of 0.05 and a power of 0.80, we calculated a minimum participant number of 26 per treatment group. This sample size underestimates our needed sample size due to substantial differences from our planned trial. Considering the up to fourfold lower selenium treatment in our trial, we felt it was prudent to quadruple the number (=100) and then double it to accommodate our larger age range, shorter duration, and loss to follow-up, arriving at the final participant number of 200.

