### Data analysis

Data are stored in a password-protected database at icddr,b, through a platform that allows sharing of data between project investigators (PIs) at icddr,b and the University of Calgary. Statistical analyses will be done using the statistical software SPSS for Windows PASW version 20. Normality and homogeneity of variances will be determined. Data not normally distributed will be transformed as necessary. Initially Spearman’s correlation analyses will evaluate univariate association between arsenic exposure (urinary and hair arsenic) and outcome variables (oxidative stress, antioxidant status, lung inflammatory status, and genetic variables). Covariates (e.g., demographic and socioeconomic variables, morbidity, daily diet, and BMI of participants) will be evaluated for significant association with exposure and outcomes. Missing data are excluded from that specific analysis. Significantly correlated variables will be further analyzed in multiple linear regression models controlling for potential confounding variables stratified by sex. Potential confounders will be identified based on correlations (*p* < 0.15) with the exposure (toxic metal) and outcomes and will be included in the final models when they change the effect estimate for metal exposure on the outcome by 5 % or more.

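### The primary outcome is stated in four different ways with no rule for combining its parts, only hair arsenic was sized, and the analysis section treats hair and urinary arsenic as exposure

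*Protocol article*

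**What the plan says.** The article describes the primary outcome in four places.

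- Abstract, Methods/design: "The major outcome will be arsenic excretion in urine and feces, as well as arsenic deposition in hair and morbidity outcomes". This gives four components.
- Trial objectives: the diet "can decrease the body burden of arsenic, evident by higher excretion in urine and/or feces and decreased deposition in hair". Morbidity is absent, and a direction is given for each matrix.
- Table 1, primary outcome row: arsenic body burden "by measurement of As excretion in urine and feces and deposition in hair". This gives three components, without morbidity.
- Discussion: arsenic body burden as a single construct, with no matrix named.

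Three other sections bear on the point. Sample size is "based on a one-sided effect for arsenic concentration in hair", with type I error 0.05 and power 0.80. Study procedures limits stool collection to a subset of about 40 participants. Data analysis begins with Spearman correlations to "evaluate univariate association between arsenic exposure (urinary and hair arsenic) and outcome variables", lists morbidity among the covariates, and selects confounders by how far they move the estimated effect of the metal on the outcome.

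On mechanism, the Background says that "selenium interacts with arsenic to form a complex which is excreted in the bile".

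**The concern.** A reader cannot tell from the article which result would make the trial positive. The four descriptions differ in their components, and none says whether all components, some of them, or hair plus one excretion measure must succeed. Hair is the only component with a sample size behind it.

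The roles of the variables also conflict. Under Trial objectives, urinary and hair arsenic are results of the intervention. Under Data analysis they are explanatory variables for oxidative stress, antioxidant status and lung inflammation. Morbidity is a major outcome in the Abstract and an adjustment variable in the analysis. The models described do not estimate the randomized comparison that the hypothesis is about.

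At stake is whether a positive claim can be recognized as the one planned. The Discussion intends the results to inform government policy on lentil imports, so this should be settled before outcome data are seen.

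**Working it through.** **1. The plan's own figure.** Inputs from Sample size: means 2.01 and 1.23 μg/g, SDs 1.4 and 0.73, alpha 0.05, power 0.80.

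n per group = (SD₁² + SD₂²) × (z₁₋α + z₀.₈₀)² / difference²

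- One-sided: (1.96 + 0.5329) × (1.645 + 0.842)² / 0.78² = 25.33, rounded up to 26. The stated 26 reproduces.
- Two-sided: 32.16, rounded up to 33.

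The stated figure is therefore one one-sided test of one variable, hair. For scale, dividing alpha equally by Bonferroni would raise the starting figure of 26 to 33 for two components (0.025), 37 for three (0.0167) and 39 for four (0.0125).

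**2. Error under the strict reading of the objective.** In Trial objectives, *and/or* joins only urine and feces; hair is attached by *and*. Success then needs hair together with urine or feces.

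- Since hair must reject at 0.05, the error when no component is affected is at most 5%.
- With independent components it is 0.05 × (1 − 0.95²) = 0.05 × 0.0975 = 0.0049, or 0.49%.

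There is no inflation under this reading.

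**3. Error if any one component sufficed.** With k independent tests at 0.05 the chance of at least one false positive is 1 − 0.95ᵏ. For correlated tests an equicorrelated multivariate normal was used, one-sided. The correlations are assumptions, since the article gives none.

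| Components | Correlation 0 | 0.5 | 0.9 |
|---|---|---|---|
| 3 (urine, feces, hair) | 14.3% | 11.8% | 8.0% |
| 4 (with morbidity) | 18.5% | 14.4% | 8.8% |

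**4. What feces could show.** The article gives no fecal effect size. Assume about 20 stool participants per group, borrow the standardized hair effect (0.78 / 1.1164 = 0.70, where 1.1164 is the root-mean-square of the two SDs), and ignore household clustering. Power is then about 71% at one-sided 0.05 and 53% at 0.0167.

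**5. Roles side by side.**

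| Variable | Abstract, objectives, Table 1 | Data analysis |
|---|---|---|
| Urinary arsenic | Outcome; higher is evidence of benefit (objectives) | Exposure |
| Hair arsenic | Outcome; lower is evidence of benefit (objectives) | Exposure |
| Morbidity | Major outcome (Abstract only) | Covariate |
| Randomized lentil group | The comparison of interest | Not the effect estimated in the models described |

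**6. Mechanism.** Biliary excretion supports the fecal route. It does not by itself establish that higher urinary arsenic is a benefit.

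**The case against.** The strongest reply is that the article names one construct, arsenic body burden, in Table 1 and the Discussion, and that the matrices are ways of measuring it. The Abstract says major rather than primary, so the morbidity mismatch may be loose wording. The objective, read as written, requires hair. A condensed article may also leave the handling of several outcomes to an analysis plan that is not shown.

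Much of this stands, and it rules out several stronger readings:

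- A reader might infer that success may be claimed on any component, so that the error is 14% or 19%. The objective does not say that. Those figures also need independence, which is doubtful for measures of one construct.
- A reader might infer that error control is absent. The article's silence does not show this.
- A reader might infer that urine will go uncorrected for dilution because only a 15–20 ml sample is described. Such detail may sit in a laboratory manual or analysis plan, and nothing here excludes it.
- A reader might infer that a rise in urinary arsenic counts as harm under Data analysis, or that the mechanism predicts a fall in urine. The text says neither.

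What the reply does not remove is the conflict in the text itself. A further document can add detail, but it cannot make these descriptions agree or undo the change of roles in Data analysis.

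**Conclusion.** The point holds as an inconsistency in what the article states. The components differ between the Abstract, Trial objectives, Table 1 and the Discussion, and no section fixes how they combine. Only hair was sized, and the same section structure makes two primary measures into exposures and a major outcome into a covariate. The models described estimate metal effects, not the effect of randomized group.

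The effect on error is conditional. It is none under the strict reading of the objective. It is about 8–14% (three components) or 9–19% (four) against 5% if any component could carry the claim, for assumed correlations from 0.9 to 0. The article does not adopt that second rule, but it does not exclude it either. The textual conflict rests on no assumption; the fecal power figures rest on a borrowed effect size, an equal split and no clustering.

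**What to change.** - Name hair arsenic at 6 months as the single primary outcome in the Abstract, Trial objectives and Table 1. It is the only outcome the trial was sized on.
- Make urinary and fecal arsenic supportive secondary outcomes, tested two-sided, with no claim of benefit from urine alone.
- List morbidity as a secondary outcome.
- Amend Data analysis so that the primary analysis compares hair arsenic by randomized lentil group, and label the exposure–outcome correlations and regressions exploratory. Without this step the new primary outcome would still be classed as an exposure.

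Requiring a stated combination of components would also remove the ambiguity, but feces is available in only about 40 participants and urine was not sized.

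The cost is mostly wording, with no added samples. The downside is that a positive urine or feces result alone no longer counts as success. Because recruitment is under way, the change also needs notice to the ethics boards and a dated, justified registry update, made before outcome data are examined.

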**Discussion:**

Selenium pills as a treatment for arsenic exposure are costly and inconvenient, whereas a whole food approach to lower the toxic burden of arsenic may be a practical remedy for Bangladeshi people while efforts to provide safe drinking water are continuing. If high-selenium lentils prove to be effective in counteracting arsenic toxicity, agronomic partnerships between Canada and Bangladesh will work to improve the selenium content of the Bangladeshi-grown lentil crops. Results will be presented to the community to promote informed food choices, which may include increasing selenium in their diet.

**Trial registration:**

ClinicalTrials.gov NCT02429921

**Electronic supplementary material:**

The online version of this article (doi:10.1186/s13063-016-1344-y) contains supplementary material, which is available to authorized users.

## Background

In the 1970s, the United Nations International Children’s Emergency Fund (UNICEF) and the Bangladeshi government, followed by private initiatives, installed millions of tube wells in rural Bangladesh in an effort to reduce infant and child mortality caused by water-borne diseases such as cholera and other diarrheas [1, 2]. Tragically, many of these deeper wells contained arsenic, which leaches from the bedrock into the groundwater. It was not until the 1990s, when people developed previously unknown skin lesions, that more extensive well water testing revealed the scale and severity of the arsenic problem. By then millions of people had been exposed to arsenic for more than 20 years [3].

In 2002, the World Health Organization (WHO) described the case of Bangladesh as “the world’s largest mass poisoning of a population in history…” [4]. At that time it was estimated that between 35 and 77 million people were exposed to dangerously high concentrations of arsenic — above the WHO guideline of 10 ppb and frequently above the national standard in Bangladesh of 50 ppb. It is noteworthy that food such as rice is irrigated with arsenic-contaminated shallow tube well water, potentially adding to the toxic burden [5].

The annual cost to treat arsenic-related health problems in Bangladesh is currently estimated at up to $77.5 million [6].

A number of studies have found an association between the detrimental effects of arsenic exposure and malnutrition [7–9], which is also a prominent health concern in the Bangladeshi population, especially in children [10]. Chen et al*.* found that the risk of developing arsenic-related skin lesions was greatly enhanced with low blood selenium. Selenium and arsenic work antagonistically in the body by competing in many biological functions [11]. In the blood, selenium interacts with arsenic to form a complex which is excreted in the bile [12], thereby lowering the arsenic body burden. Thus, higher selenium intake may be crucial to combat arsenic toxicity. Selenium levels in food are dependent on selenium bioavailability in the soil. Limited data are available on the selenium content of soils in Bangladesh. Initially it was found that agricultural soil in Bangladesh (*n* = 19) contains good selenium levels [13]. However, the authors determined that only 12 % of selenium was soluble, reducing the immediately available selenium to 0.12 μg/g. A ”nutritional selenium deficiency” in soil is < 0.5 μg/g soil [14]; therefore, Bangladeshi soil falls into the selenium deficient category. The US dietary recommended daily allowance (US-RDA) for selenium for an adult is 55 μg/day [15], and Spallholz et al*.* (2008) estimated that Bangladeshis consume about 26 μg/day [13], approximately half of the RDA.

Supplementation of selenium in pill form is currently recommended to treat arsenicosis. However, pills are not often well received by people and are expensive for low-income families. Lentils are a very common food in Bangladesh, with the major lentil imports coming from Canada, a world leader in lentil exports. In crop year 2011/2012, 47,620 tonnes (metric tons) of lentils were exported to Bangladesh, and in 2012/2013 this increased to 90,800 tonnes (metric tons) [16]. Saskatchewan (SK) grown lentils are naturally rich in selenium, mostly in the form of L-selenomethionine, which is highly bioavailable [17]. Saskatchewan lentils have mean selenium levels between 425–672 μg/kg, with the levels in some regions as high as 1884 μg/kg [18]. Experimental studies in animal models demonstrated that diets made of high-selenium lentils counteract arsenic toxicity and reduce arsenic-related atherosclerosis [19, 20]. Incorporated into the daily meals of arsenic-exposed Bangladeshi families, high-selenium lentils may help mitigate the symptoms of long-term arsenic poisoning in a cost-effective, culturally acceptable, and nutritionally beneficial way.

### Trial objectives

The hypothesis of the trial is that consumption of high-selenium lentils from Saskatchewan, Canada, will reduce the body burden of arsenic and decrease arsenic toxicity in a chronically arsenic-exposed Bangladeshi population compared to those consuming low-selenium lentils.

The primary objective was to perform a double-blind, randomized controlled trial to determine whether incorporation of high-selenium lentils into the daily diet, providing at least the RDA of Se (55 ug), can decrease the body burden of arsenic, evident by higher excretion in urine and/or feces and decreased deposition in hair, compared to the treatment group on low-selenium lentil consumption. Secondary objectives were to determine if consumption of high-selenium lentils:improves antioxidant statusreduces oxidative DNA damagechanges acute phase proteins as well as serum lipid levels in arsenic-exposed individualsdecreases arsenic-related lung inflammation measured using exhaled nitric oxide as an indirect indicatorimproves the body mass index (BMI) and blood pressure of arsenic-exposed individuals

Herein, we describe the design and methods protocol for our 3-year study now underway.

## Methods/design

This trial protocol has been approved by the University of Calgary’s Conjoint Health Research Ethics Board (Ethics ID: REB13-1211-Mod3), the University of Saskatchewan’s Biomedical Research Ethics Board (Bio-No. 14-212), plus the Research Review Committee, the Ethics Review Committee, and the Data and Safety Monitoring Board (DSMB) of the International Centre for Diarrhoeal Disease Research, Bangladesh (Icddr,b) (Protocol No. PR-14013). Any changes to the trial protocol are communicated to the relevant parties and ethics boards. The trial will be reported according to SPIRIT (Standard Protocol Items: Recommendations for Intervention Trials) 2013 [21] (see Additional file 1). A summary of the trial according to the WHO Trial Registration Minimal Data Set is provided in Table 1 [22].

**Table 1 Tab1:** WHO Trial Registration Minimal Data Set according to Moja et al*.* [22]

Data	Information
Trial identification number	ClinicalTrials.gov NCT02429921
Trial registration date	April 21, 2015
Secondary IDs	REB13-1211 (CHREB, University of Calgary), PR-14013 (ERC, icddr,b)
Funding sources	Global Institute for Food Security (GIFS); Grand Challenges Canada - Stars in Global Health Round 5
Primary sponsor	[name], Faculty of Vet. Med, University of Calgary, Canada
Secondary sponsor	RR, icddr,b, Dhaka, Bangladesh
Responsible contact person	RR, icddr,b; [contact]
Research contact person	[name], Faculty of Vet. Med., University of Calgary; [contact]
Brief title of the study	High-selenium Lentils Versus Arsenic Toxicity
Official title of the study	Mitigating arsenic toxicity in Bangladeshi people by supplementing their diets with high selenium lentils
Country of recruitment	Bangladesh
Health problem studied	Chronic arsenic poisoning
Intervention	High-selenium lentils, control: low-selenium lentils
Key inclusion and exclusion criteria	Inclusion criteria: families with >100 ppb As in their well water; ages eligible for study: 14–75
	Exclusion criteria: As content of well water ≤100 ppb; ill health detected during initial recruitment health check
Study type	Double blind, parallel, block-randomized, controlled intervention trial
Trial start date	September 28, 2015
Target sample size	200 per treatment group (400 in total)
Recruitment status	Active
Primary outcome	Arsenic body burden: We will determine if high-Se lentil consumption will decrease the body burden of As by measurement of As excretion in urine and feces and deposition in hair
Key secondary outcomes	We will determine if high-Se lentils:
	1. Increase concentrations of protective antioxidants and reduce oxidative stress and acute phase response in blood
	2. Modulate serum lipid profile and blood pressure
	3. Reduce As-related lung inflammation

